## Abstract

**Introduction::**

A novel coronavirus, tentatively designated as 2019 Novel Coronavirus (2019-nCoV), now called severe acute respiratory syndrome coronavirus 2, emerged in Wuhan, China, at the end of 2019 and which continues to expand. On February 11, 2020, the World Health Organization (WHO) named the disease coronavirus disease 2019 (COVID-19). On February 28, WHO increased our assessment of the risk of spread and the risk of impact of COVID-19 to very high at a global level. The COVID-19 poses significant threats to international health.

Computed tomography (CT) has been an important imaging modality in assisting in the diagnosis and management of patients withCOVID-19. Some retrospective imaging studies have reported chest CT findings of COVID-19 in the past 2 months, suggesting that several CT findings may be characteristic. To our knowledge, there has been no prospective multicentre imaging study of COVID-19 to date.

We proposed a hypothesis: There are some specific CT features on Chest CT of COVID-19 patients. And the mechanism of these CT features is explicable based on pathological findings.

**Objective::**

To investigate the specific CT features of COVID-19 and the formation mechanism of these CT features.

**Method::**

This study is a prospective multicenter observational study. We will recruit 100 patients with COVID-19 at 55 hospitals. All patients undergo chest CT examination with the same scan protocol. The distribution and morphology of lesions on chest CT, clinical data will be recorded. A number of patients will be pathologically examined after permission is granted. The data of these three aspects will be analyzed synthetically.

**Discussion::**

This study will help us to identify the chest CT features of COVID-19 and its mechanism.

**Ethics and dissemination::**

This retrospective study was approved by the Biomedical Research Ethics Committee of West China Hospital of Sichuan University (No. 2020–140). Written informed consent will be obtained from all study participants prior to enrollment in the study. To protect privacy of participants, all private information were kept anonymous. The results will be published in a peer-reviewed journal and will be disseminated electronically and in print regardless of results.

## Introduction

1

A novel coronavirus, tentatively designated as 2019 Novel Coronavirus (2019-nCoV),^[1]^ now called severe acute respiratory syndrome coronavirus 2,^[2]^ emerged in Wuhan, China, at the end of 2019 and which continues to expand. On February 11, 2020, the World Health Organization (WHO) named the disease coronavirus disease 2019 (COVID-19). On February 28, WHO increased our assessment of the risk of spread and the risk of impact of COVID-19 to very high at a global level.^[3]^ As of 24:00 on March 6, the National Health Commission had received 80,651 reports of confirmed cases and 3070 deaths, and in all 55,404 patients had been cured and discharged from hospital. There still remained 22,177 confirmed cases (including 5489 in serious condition) and 502 suspected cases. So far, 672,458 people have been identified as having had close contact with infected patients. 26,730 are now under medical observation.^[4]^ The WHO reported 17,481 laboratory-confirmed cases and 335 deaths in 88 countries /territories/areas as of March 6, out of China.^[5]^ The COVID-19 poses significant threats to international health.

Computed tomography (CT) has a major role in both diagnosis and categorization of COVID-19 on the basis of case definitions issued by the WHO and the treatment guidelines from the National Health Commission of the People's Republic of China. Almost all suspected patients receive chest CT scan. Some retrospective imaging studies have reported chest CT findings of COVID-19 in the past 2 months, suggesting that several CT findings may be characteristic.^[6–18]^ To our knowledge, there has been no prospective multicentre imaging study of COVID-19 to date.

We proposed a hypothesis: There are some specific CT features on Chest CT of COVID-19 patients. And the mechanism of these CT features is explicable based on pathological findings.

## Participants and methods

2

### Study aims

2.1

The aim of this study is to investigate the specific CT features of COVID-19 and the formation mechanism of these CT features.

**Figure 1 F1:**
[figure not shown]
A flowchart of the study. COVID-19 = disease coronavirus disease 2019, CT = computer tomography, RR = respiratory rate, SpO2 = percutaneous oxygen saturation.

### Study registration

2.3

This clinical trial has been registered on the Chinese Clinical Trial Registry (www.chictr.org.cn), and the registration number is ChiCTR2000029764.

### Eligibility criteria

2.4

#### Inclusion criteria

2.4.1

We will include patients who are eligible according to the following criteria:

1.The patient will be confirmed to be COVID-19 by laboratory examination.2.Undergo chest CT scan during the treatment and at least 1 chest CT scan during follow-up.3.Written informed consent to participate in the study.4.Compliance with the study regulations.

#### Exclusion criteria

2.4.2

1.CT image quality does not meet the analysis criteria.2.Pregnant and lactating women.

### Recruitment

2.5

We will recruit 100 patients with COVID-19 at 5 hospitals. The researcher will explain the aim of this study and the details of the procedures and will obtain informed consent from potential subjects prior to the collection of information. Participants will be free to withdraw at any time during the study, and this will not affect their clinical treatment.

### Intervention

2.6

This is an observational study. There are no interventions in this study. The researchers also do not influence the doctors who actually write the diagnosis reports.

### CT procedure

2.7

#### CT scanning protocol

2.7.1

The CT scanning protocol of these 5 hospitals adopted the same parameters: tube voltage, 120 kV; tube current, 110mAs (automatic adjustment); rotation time, 0.5 second; section thickness, 0.75 mm; collimation, 0.6 mm; pitch, 1; matrix, 512 × 512; and inspiration breath hold. Reconstruction was performed with a bone algorithm with a thickness of 1 mm and an interval of 1 mm. All scans will be obtained with the patient in the supine position during end-inspiration without intravenous contrast material. The following windows will be used: a mediastinal window with a window width of 350 HU and a window level of 40 HU and a lung window with a width of 1800 HU and a level of 400 HU.

#### CT features analysis

2.7.2

All CT images will be reviewed by 2 radiologists with 10 years of experience each ([name] and [name]) independently, and final decisions will be reached by consensus. For disagreement between the 2 primary radiologist interpretations, a third radiologist with 15 years of experience ([name]) adjudicated a final decision.

The distribution of lung abnormalities will be recorded as:

1.Left, right, or bilateral lung;2.Predominantly subpleural, hilar, and random;3.Predominantly superior, inferior, and random;4.Predominantly anterior, posterior, and random;5.Presented as a solitary lesion. Numbers of involved lobes and segments of lungs were recorded also.

The CT findings will be described using internationally standard nomenclature defined by the Fleischner Society glossary, including ground glass opacity, consolidation, crazy-paving pattern, bronchiolectasis, interlobular septal thickening, and lymphadenopathy. Other abnormalities will be noted.

### Clinical data collection

2.8

All the clinical data on epidemiology, signs and symptoms, underlying comorbidities, and laboratory results will be extracted from electronic medical records and checked. The real-time reverse transcriptase polymerase chain-reaction test will be performed. The date of disease onset will be defined as the day when the symptom noticed.

### Pathologic procedure

2.9

If the patient agrees, we will conduct biopsy pathology. If the deceased signed the body donation while alive, we can perform autopsy to obtain the pathological results.

### Outcome measure

2.10

The primary outcome of this study is to reveal the characteristic imaging features of COVID-19. The secondary outcome is to reveal the imaging features at different pathological stages.

### Data collection and management

2.11

Data will be processed anonymously, omitting the information that can identify the participant's individual identity. Strict safety and confidentiality measures will be established in the archives of clinical trial institutions.

### Sample size calculation

2.12

We calculated the number of patients needed considering the rates of major imaging findings in several published retrospective imaging studies of COVID-19; the estimated sample size is 80 participants according to Lehr's formula. We will recruit 100 patients considering the dropout rate of 20%.

### Statistical analysis

2.13

For variables with a normal distribution, the independent Student's t test was used. For abnormal distributional variables, the Mann–Whitney *U* test was used. The frequency of CT signs was expressed as the number (percentage) of occurrences and was compared for cases of early- versus advanced-phase disease using the chi-square test or the Fisher exact test. The variables included in the analysis will be subject to single-factor logistic regression, and all variables with significant characteristics will be selected for binary or multiple logistic regression analysis to obtain independent predictors within the group. Finally, the independent predictors in the 2 groups were combined into binary logistic regression analysis to obtain the independent predictors in all variables. For all binary logistic regression analyses, odds ratio and 95% confidence intervals of independent predictors were calculated and model function equations, sensitivity, specificity, and area under the curve were given. Backward stepwise selection was utilized based on the Akaike information criterion.

All statistical analyses were performed with SPSS 20.0 (IBM, Armonk, NY, USA). A 2-tailed *P* value lower than .05 was considered statistically significant.

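### Univariable P<.05 screening of many candidates in about 80 patients will often yield false independent predictors and an optimistic AUC

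*Protocol article*

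**What the plan says.** Section 2.13 (Statistical analysis) of the protocol article fixes this sequence:

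- Every variable is tested in a single-factor logistic regression.
- Next, "all variables with significant characteristics will be selected for binary or multiple logistic regression analysis to obtain independent predictors within the group". The only significance level in the section is the general one: "A 2-tailed *P* value lower than .05 was considered statistically significant".
- The survivors of two groups are put into a further logistic model. The groups are not defined there; they are read here, as an assumption, as CT variables and clinical variables.
- On elimination: "Backward stepwise selection was utilized based on the Akaike information criterion".
- For these models, odds ratios with 95% CIs are calculated and "model function equations, sensitivity, specificity, and area under the curve were given".

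Section 2.12 (Sample size calculation) gives the size: "the estimated sample size is 80 participants according to Lehr's formula", raised to 100 for dropout.

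Section 2.7.2 (CT features analysis) lists 5 distribution items, lobe and segment counts, and 6 named findings, and leaves room for other abnormalities. Section 2.8 (Clinical data collection) adds epidemiology, symptoms, comorbidities and laboratory results without giving a number.

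**The concern.** The number of variables tested at the first step is large for the number of patients. Each unrelated variable has about a 5% chance of passing the screen, and one that passes is then carried forward as a candidate predictor. Odds ratios of variables chosen because they looked large are biased away from 1. Conventional 95% CIs fitted after selection treat the chosen model as if it had been known beforehand. An AUC computed on the patients who drove the selection is too high.

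The aim in section 2.1 is to find specific CT features, and the Discussion hopes to address the predictive value of baseline CT. A reader could take a model equation with an AUC near 0.7 as an answer to that question when noise alone can produce it.

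**Working it through.** **The plan's own figure.** 80/(1 − 0.20) = 100, so the step from 80 to 100 reproduces. The 80 cannot be checked, because no rates are given. Lehr's formula, n per group = 16·p̄(1−p̄)/d², with 40 per group gives d = √(16·p̄(1−p̄)/40). That is 0.25 at p̄ = 0.2 and 0.32 at p̄ = 0.5. The formula sizes a two-group comparison, not a prediction model.

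**Inputs.**
- From the document: 80 analysable patients (2.12); two-sided .05 (2.13); CT candidates 5 + 2 + 6 = 13 (2.7.2).
- Assumed: outcome split 40/40, with 20/60 as a check; 10 to 30 clinical candidates, with a deliberately small 6+6 case. The logistic outcome is not defined; early versus advanced phase is the only contrast the section names.
- Patients in the smaller group per candidate: 40/13 = 3.1 for CT alone; 40/33 = 1.2 with 20 clinical variables added.

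**The screen by formula.** For K independent null tests, the chance of at least one hit is 1 − 0.95^K: 49% for K = 13, 69% for K = 23, 82% for K = 33, 89% for K = 43.

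**Why the later steps do not remove the false hit.** Backward AIC drops a one-parameter term only if its likelihood-ratio chi-square is below 2 (P above .157). A variable that passed a likelihood-ratio screen at .05 has a chi-square above 3.84 on its own, so AIC cannot empty the model. Whether any predictor is declared is therefore settled at the screen.

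**The full procedure under the null.** Two simulations, 1000 studies per case, with every variable unrelated to outcome: screen at .05, backward AIC within each group, then backward AIC on the survivors. They differ in the screening test and in the mix of binary and continuous variables. The AUC is the mean among studies that end with a model.

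| Candidates (CT + clinical) | Setting | Screen | At least one predictor | Mean apparent AUC |
|---|---|---|---|---|
| 13 + 0 | n=80, 40/40 | likelihood ratio | 51% | 0.64 |
| 13 + 12 | n=80, 40/40 | likelihood ratio | 75% | 0.67 |
| 13 + 20 | n=80, 40/40 | likelihood ratio | 84% | 0.69 |
| 13 + 20 | n=80, 20/60 | likelihood ratio | 83% | 0.72 |
| 6 + 6 | n=80, 40/40 | Wald | 41% | 0.65 |
| 13 + 10 | n=80, 40/40 | Wald | 64% | 0.66 |
| 13 + 20 | n=80, 40/40 | Wald | 76% | 0.68 |
| 13 + 30 | n=80, 40/40 | Wald | 86% | 0.70 |
| 13 + 20 | n=80, 20/60 | Wald | 75% | 0.70 |
| 13 + 20 | n=80, 40/40, correlation 0.3 | Wald | 70% | 0.67 |
| 13 + 20 | n=100, 50/50 | Wald | 76% | 0.66 |

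The true AUC is 0.50 throughout; in the Wald runs, AUC on 4000 fresh subjects averaged 0.50. In the 13+20 Wald case at n=80, 40/40, the apparent AUC ran from 0.60 to 0.79 (5th to 95th percentile), and 43% of studies kept two or more predictors. Monte Carlo error is at most √(0.5·0.5/1000) = 1.6 percentage points.

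The simulated frequencies follow the formula: 51% against 49% for 13 variables, and 76% to 84% against 82% for 33.

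**The case against.** Several stronger readings are tempting, and the document does not support them.

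- **That the three rounds cause the problem.** They do not drive the false-predictor rate. The formula for the screen alone nearly reproduces the simulated frequencies, and rounds two and three mainly prune.
- **That the section states two conflicting retention rules.** Significance governs entry to the multivariable models and AIC governs elimination afterwards. These are successive steps and are compatible.
- **That false predictors are bound to appear.** In the Wald null cases, 14% to 59% of studies end with none. Often is the right word.
- **That about 84% is the expected rate.** It rests on an assumed 20 clinical variables and independent predictors. With a Wald screen the same case gives 76%, and with correlation 0.3 it gives 70%. Section 2.7.2 lists overlapping items (laterality, solitary lesion, lobe and segment counts), so some correlation is likely. The count that comes from the document, 13, gives 51%.
- **That the lack of a named validation step is itself an error.** This is a condensed article, and a fuller plan may add resampling. The article does not say that the AUC is left uncorrected.
- **That the equation must fail in new patients.** The simulations cover only the case where nothing is related to outcome. If some variables matter, part of the discrimination would be real.

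It is also fair that the outcomes in section 2.10 are framed as revealing imaging features and that no clinical use of the equation is proposed. What remains is the screening rule. It is stated, not omitted, and a later validation step would expose its effect without removing it.

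**Conclusion.** The point holds in limited form. Univariable screening at .05 followed by selection and conventional reporting, in about 80 patients, will often declare independent predictors where none exist, with an AUC that looks moderate. Under the null this happens in about half of studies with the 13 CT variables alone (mean apparent AUC about 0.64, true 0.50), and in about 64% to 86% (AUC 0.66 to 0.70) with 10 to 30 clinical variables added.

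The size rests on an assumed 40/40 split, the assumed number of clinical variables, independent predictors, and the reading of the two groups as CT and clinical. Changing the split to 20/60, adding correlation or raising n to 100 shifts the figures but not the conclusion. The CIs and performance measures as described take no account of the selection. The descriptive frequencies of CT signs are unaffected; the predictor and AUC claims are what would mislead.

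**What to change.** Drop the univariable significance screen and fit one model, in one of two ways:

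- a short set of predictors listed before the data are seen, about 4 parameters for about 40 patients in the smaller group (40/4 = 10 per parameter); or
- penalised logistic regression on all candidates.

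Report AUC, sensitivity and specificity corrected for optimism by bootstrap, with at least 500 resamples and every selection step repeated in each one. Label the model exploratory. State the outcome of the logistic models and what the two groups of variables are.

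The cost is some wording and a few hours of programming, possibly outside SPSS. No further patients, scans or data are needed. The reported AUC will be lower.

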### Ethics and dissemination

2.14

This retrospective study was approved by the Biomedical Research Ethics Committee of West China Hospital of Sichuan University (No. 2020–140). Written informed consent will be obtained from all study participants before enrollment in the study. To protect privacy of participants, all private information were kept anonymous. The results will be published in a peer-reviewed journal and will be disseminated electronically and in print regardless of results.

## Discussion

3

The CT features of COVID-19, reported by these retrospective chest CT studies, are variable, including both relative specificity and nonspecific. We need to know more about this novel highly contagious viral pneumonia: the correlation of CT findings with clinical severity and progression, the predictive value of baseline CT or time changes in disease outcomes, and the correlation of covid-19 with sequelae of acute lung injury remain to be investigated. We hope our research will reveal these issues.

The main limitation of our study is that we could not estimate how many patients would be willing to undergo biopsy and how many families would be willing to donate bodies.
